### Interventions

The total duration of the intervention will be 2 weeks, regardless of group allocation.

#### Functional splinting

The functional splint used in this study will be a wrist cock-up splint, with the addition of a thumb support or supination wrap if deemed appropriate for the individual child. The wrist splint will be made from thermoplastic alone or a combination of neoprene and thermoplastic. The decision to make a splint from thermoplastic alone, or a combination of thermoplastic and neoprene, will be made taking into consideration the level of support required at the wrist, the participant’s goals, and the participant’s aesthetic preference. Aesthetic preference was taken into consideration in order to improve compliance [43], and to remain consistent with considerations that would be applied in regular therapeutic situations. A thermoplastic wrist extension support on the palmer surface will be a consistent component of all splints. The wrist cock-up splint will aim to support the wrist in approximately 20 to 30 degrees of extension, however, where this amount of extension is unable to be achieved, the splint will be positioned in maximum wrist extension that is tolerable to the participant, whilst allowing for functional use of the hand. A thumb support will be included for participants whose thumb metacarpophalangeal is adducted, when the thumb position is deemed to impact on grasp and release or the child’s individual goal achievement. A supination strap will be added to the splint for children who are unable to actively supinate beyond neutral, and where supination is deemed an important prerequisite for the child’s identified goals.

#### The cognitive orientation to occupational performance (CO-OP)

Task-specific training will be carried out utilising the CO-OP approach. The standard CO-OP protocol comprises 12 sessions, with the initial session involving assessment and goal setting, subsequent 10 sessions focussed on teaching and utilising the global strategy goal-plan-do-check and the final session reviewing goals and encouraging carry-over of strategy use beyond the treatment period. For in depth details of CO-OP, the full protocol should be reviewed [29].

In the current study, general principles of the intervention will follow the CO-OP protocol, with some adaptations. During the screening process, parents will be provided with general information regarding the CO-OP approach and informed that a parent is expected to be present at all treatment sessions. The initial assessment will be an individual session in which each child will identify 3 goals related to hand function, nominating one goal that is most important to them. If participants are randomised to receive CO-OP, a more indepth discussion with parents regarding CO-OP will occur. CO-OP will be conducted in a group setting, for a total of 10 treatment sessions (5 times per week for 2 weeks). Groups will consist of 2-4 participants and each session will run for approximately 1 hour. A parent/carer will be required to be present at every session. The first group session will focus on educating parents regarding the goal-plan-do-check strategy, and introducing children to the strategy, through the use of a puppet – Captain Goal-Plan-Do-Check. Subsequent sessions will focus on the use of goal-plan-do-check for motor-based tasks, as a group at the beginning of each session, then individually with the assistance of parents throughout the session. The therapist will demonstrate the use of goal-plan-do-check and prompt parents to support children to utilise this strategy. Children will identify one goal that is most important to them, and, where possible, the whole group will work on this goal.

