#### Therapeutic considerations

Group intervention was chosen for cost and time efficiency. The CO-OP approach can be utilised in a group format [29] and task-specific training intervention provided in a group setting has been shown to be effective in this population [5,44]. The benefits of group intervention may include improved motivation and participation [44]. The treating therapist will apply generalised therapeutic considerations during the groups, as would be applied in standard practice. These will include adapting the group structure, modifying tasks, providing further assistance to children/parents who require it and implementing behavioural management strategies.

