### Statistical methods

Participant attributes will be analysed using descriptive and inferential statistics to assess baseline comparability among the 3 treatment groups. Comparison of differences between the 3 groups in the randomised controlled trial will be analysed using multiple regression analysis, with statistical significance set at p < 0.05. Statistical analysis in RCT1 will be conducted using 2 group comparisons on all participants, based on the BBT (T1 vs T2). Data from all randomised participants will be conducted on an intention to treat basis. Where outcome data are unavailable, previous scores will be carried over for analysis. Statistical analysis for RCT2 will be conducted at 2 weeks (T3) and 10 weeks (T4) compared to (T1) baseline scores, analysing between group differences. Primary analyses at T3 and T4 will be based on the COPM and GAS scores. Secondary analysis will use the same data analytical methods for scores on the BBT and range of motion for T3 only.

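### CO-OP is delivered in therapy groups of 2-4 in two of the three arms, but the stated RCT2 analysis and sample size treat all children as independent

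*Protocol article*

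**What the plan says.** The CO-OP section of the Protocol article fixes group delivery: "CO-OP will be conducted in a group setting, for a total of 10 treatment sessions (5 times per week for 2 weeks"), and "Groups will consist of 2-4 participants and each session will run for approximately 1 hour". Children choose a most important goal and, "where possible, the whole group will work on this goal". Sessions are only partly communal. They run "as a group at the beginning of each session, then individually with the assistance of parents throughout the session", and "A parent/carer will be required to be present at every session". Under Therapeutic considerations the therapist's adjustments include "adapting the group structure, modifying tasks".

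Study procedures gives CO-OP to two arms (combined with a splint, and alone). It describes daily practice with the splint, and no group sessions, for the splint-alone arm. It does not say whether a therapy group holds children from one CO-OP arm or from both.

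Statistical methods names the model: "Comparison of differences between the 3 groups in the randomised controlled trial will be analysed using multiple regression analysis", at the 0.05 level. Sample size gives 15 children per arm, 80% power and an effect size of 0.9, with group allocation and age as the two covariates. Neither section mentions the therapy group, an ICC or a design effect.

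**The concern.** Ordinary multiple regression assumes that residuals are independent and have the same variance in every arm. Children who spend ten sessions in the same small group, sometimes working on the same goal, may end up more alike than children from different groups. Splint-alone children have no such link. If so, the model gets the standard errors of contrasts involving the CO-OP arms wrong.

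The contrast most exposed is combination versus training alone. Hypothesis 1 expects comparable improvement in these two arms, and a claim of comparability depends directly on the width of the confidence interval. An interval that is too narrow or too wide would mislead on the trial's main question.

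**Working it through.** **Inputs.** From the Protocol article: 15 children per arm, therapy groups of 2-4, effect size 0.9, significance level 0.05, target power 80%. Assumed: ICC 0.05-0.20, since the document gives none.

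**The plan's own figure.** The per-arm size for two means is n = 2(z_alpha + z_beta)²/d².
- One-sided 0.05: 2(1.645 + 0.842)²/0.81 = 15.3, so 16 per arm. Power at 15 is 79.4%, which matches the stated 80% closely.
- Two-sided 0.05: 2(1.960 + 0.842)²/0.81 = 19.4, so 20 per arm.

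Sidedness is not stated. Neither version contains any allowance for clustering. The 79.4% is used below so that the power loss shown comes from clustering alone.

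**Single-arm therapy groups.** With m children per group, the design effect is DE = 1 + (m − 1) × ICC. The true standard error divided by the naive one is √DE for CO-OP v CO-OP and √((1 + DE)/2) for CO-OP v splint.

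| m, ICC | DE | Effective n per CO-OP arm (15/DE) | SE ratio, CO-OP v CO-OP | SE ratio, CO-OP v splint | Power, CO-OP v CO-OP |
|---|---|---|---|---|---|
| 2, 0.05 | 1.05 | 14.3 | 1.02 | 1.01 | 77.7% |
| 3, 0.10 | 1.20 | 12.5 | 1.10 | 1.05 | 72.7% |
| 4, 0.20 | 1.60 | 9.4 | 1.26 | 1.14 | 61.9% |

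**Type I error, single-arm groups.** This was simulated with 40,000 null trials per setting, 15 per arm, equal total variance in all arms, and a two-sided pooled-error t test on 42 df. For combination v training alone, as ICC goes from 0.05 to 0.20:
- groups of 2-3 (six of 2, one of 3): 5.7-8.1%
- groups of 3 (five): 6.2-10.1%
- groups of 3-4 (three of 4, one of 3): 6.6-12.0%

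For CO-OP v splint the range is 5.4-8.5%. With ICC 0 both tests return about 5%. As a hand check, m = 3 and ICC 0.10 give 2 × [1 − Φ(1.96/1.095)] = 7.4%, against about 7.1% simulated.

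**Groups mixing both CO-OP arms evenly.** The shared group effect then cancels from combination v training alone. The SE ratio becomes √(1 − ICC) = 0.97, 0.95 and 0.89 at ICC 0.05, 0.10 and 0.20, so the naive standard error is too large. Simulated type I error for mixed pairs is about 4.5% falling to 3.0%. For CO-OP v splint the naive standard error stays too small, unless each therapy group holds only one child per arm.

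**Does a cluster-aware analysis work with so few groups?** A t test on therapy-group means, with df based on the number of groups, held type I error at about 5% in the single-arm settings.

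**The case against.** The strongest reply is that a positive ICC is assumed, and several features could keep it low. Goals are set individually, COPM and GAS are scored on each child's own three goals, and much of each session is individual work with a parent. The shared goal applies only where possible and to one goal of three. The remark that group format may improve motivation describes an average benefit, not variation between groups. All of this stands, and it is why the result is given as a range. At ICC 0.05 with groups of 2-3 the test is close to nominal. None of it makes independence a safe default, because the plan gives no reason to take the ICC as zero.

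A reader might infer that the CO-OP standard errors are certainly too small and that false positives must exceed 5%. The document does not support that. For combination v training alone the direction depends on how groups are formed by arm, which is not stated. A reader might also infer that children share a parent; the text requires a parent or carer at each session and says nothing of sharing. Nor should a shortfall of power under two-sided testing be charged to clustering; that is a separate question.

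The full protocol or an analysis plan, not shown here, could add a group term. But the article does more than leave the model open: it names one that has no such term.

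Finally, with few groups the variance component is hard to estimate. With five groups of 3 per CO-OP arm, its ANOVA estimate is zero or negative with probability about 44%, 35% and 21% at ICC 0.05, 0.10 and 0.20. This is a real limitation, but it does not defeat the remedy, since an analysis with small-sample df can hold its level.

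**Conclusion.** The concern holds conditionally. The stated model and sample size ignore a nesting that the protocol itself creates in two of three arms. If the ICC is positive, inference that assumes independence is misstated:
- **Single-arm groups, ICC 0.05-0.20:** type I error of about 6-12% for combination v training alone, and about 5.4-8.5% for CO-OP v splint.
- **Evenly mixed groups:** about 4.5-3.0% for combination v training alone, so the test is conservative.

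The size is small at low ICC with the smallest groups, and material at ICC 0.10-0.20 with groups of 3-4. The figures rest on the assumed ICC range, equal total variance across arms and 15 analysed children per arm. This should be corrected, but it does not undermine the design.

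**What to change.** 1. State whether each CO-OP therapy group holds children from one arm or from both.
2. Record a therapy-group identifier for every child receiving CO-OP. Do this during delivery, since it may not be recoverable later.
3. Replace the regression named under Statistical methods with a partially nested mixed model: a random therapy-group effect for children receiving CO-OP, splint-alone children as clusters of one, separate residual variances for CO-OP and splint-alone children, and Kenward-Roger or Satterthwaite degrees of freedom. The same model serves single-arm and mixed groups. If it is not adopted, justify taking the ICC as zero.

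The cost is analysis wording and one data field. Intervals will be somewhat wider when groups are single-arm. With only about 4-7 therapy groups per arm, the group variance will be poorly estimated and sometimes zero, and the report should say so.

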#### Therapeutic considerations

Group intervention was chosen for cost and time efficiency. The CO-OP approach can be utilised in a group format [29] and task-specific training intervention provided in a group setting has been shown to be effective in this population [5,44]. The benefits of group intervention may include improved motivation and participation [44]. The treating therapist will apply generalised therapeutic considerations during the groups, as would be applied in standard practice. These will include adapting the group structure, modifying tasks, providing further assistance to children/parents who require it and implementing behavioural management strategies.

#### Reliability training of assessors and treatment administrators

The treating therapist will be an experienced occupational therapist, who has undergone formal training regarding upper limb splinting and the use of the CO-OP approach, and has experience using both of these approaches in clinical practice. All assessors (experienced occupational therapists) will undergo training regarding standardised use of outcome measures. A trial manual has been developed to ensure consistency in administration of assessments.

### Measures

#### Demographic and classification measures

Demographic information will be collected from participants prior to baseline measurement. This will include the participant’s diagnosis, age, manual abilities classification system (MACS) level, gross motor function classification system (GMFCS) level, House thumb classification, cognition, behaviour, socioeconomic information and details regarding any current or recent upper limb interventions including occupational therapy, Botulinum Toxin A injections or surgery.

##### Manual abilities classification system (MACS)

The Manual Abilities Classification System (MACS) is a system used to describe how children with cerebral palsy use their hands to handle objects in everyday activities [45]. This classifies five levels of hand use on a continuum from I (Independent with age appropriate hand tasks, able to handle objects easily and successfully) to V (Child is dependent, unable to handle objects and severely limited ability to perform simple actions) [45]. Parents and the child will be actively involved in determining the child’s MACS level to describe how the child uses their hands on a daily basis, rather than describing the child’s maximum capacity to use their hands. Although not developed for children with brain injury, the MACS is an appropriate tool to enable a consistent classification of hand function in all participants of the present study, and as such will be used to describe hand function in participants with brain injury as well as those with cerebral palsy.

##### Gross motor function classification system (GMFCS)

The Gross Motor Functional Classification System (GMFCS) is a system used to describe a child’s functional gross motor abilities [46]. The GMFCS describes five levels of motor ability from I (Independent mobility, walks without limitations) to V (Dependent for mobility, transported in an attendant-propelled wheelchair) across 3 age groups: 4-6 years; 6-12 years and; 12-18years [46]. Within the clinical setting, the GMFCS may be used as a predictive tool and would not be appropriate for use for a child with a brain injury. In this study the GMFCS will be used as a descriptive tool to gain consistent baseline information regarding gross motor ability across all study participants, regardless of diagnosis of brain injury or cerebral palsy.

##### House thumb classification

The House Thumb Classification is a tool that describes common thumb deformity [47], and has been found to be a reliable descriptor in the cerebral palsy population [48]. The assessor identifies the most appropriate thumb classification from 4 visual options, based on the position of the child’s thumb during activity.

#### Outcome measures

Primary outcome measures will measure change in the activity and participation domain of the ICF, using the COPM and GAS, and secondary outcome measures will measure changes in the body function and structure domain of the ICF, using the BBT test and wrist range of motion, as shown in Table 1. Outcome measure timepoints are reflected in Figure 1.

**Table 1 T1:** Classification of outcome measures according to the ICF model

**Outcome measures according to ICF domain**	
**Body function and structure**	**Activity and participation**
Wrist range of motion	COPM
Box & blocks test	GAS

#### Primary outcomes

##### The Canadian occupational performance measure (COPM)

The COPM is an individualised, child and family focussed tool that is used to measure change in goals that are meaningful to the individual [49]. The COPM measures change in the activities and participation domain of the ICF. The COPM is carried out as an interview, structured around the areas of self-care (dressing, toileting, feeding), leisure (hobbies/interests, sports) and productivity (school). The child and family identify areas of difficulty, prioritise these difficulties, then rate the child’s performance and satisfaction in those areas identified as most important to the child. It is the performance and satisfaction scores that are used to measure change. The 3 upper limb tasks identified as most important will be set as the goals for therapy. There is strong evidence to support the internal consistency reliability, content and construct validity and responsiveness of the COPM when used in paediatric rehabilitation [44,50]. The COPM has been shown to be responsive to change, with a 2 point improvement on performance scores recognised as clinically significant [49,51]. All participants, regardless of age, will be involved in the COPM process of identifying meaningful goals as is recognised as an important component of the CO-OP protocol [29].

##### The goal attainment scale (GAS)

The GAS is a measure of change of client-specific goals that may not be measurable through standardised assessments [50,52]. The GAS may offer children and families the opportunity to set a wider range of goals than those set using the COPM, particularly in regard to upper limb activities [50]. Following the administration of the COPM, 3 GAS goals related to upper limb function will be set. Goals will be formatted on a 5 point scale; -2 (current level of function); -1 (less than expected level of performance); 0 (expected level of performance), +1 (more than expected level of performance); +2 (much more than expected level of performance). Whilst being recognised as being responsive to change [50], there is still limited evidence supporting the reliability and validity of GAS for detecting clinically significant changes [52,53]. A change of 2 points on the GAS is generally recognised as significant (ie. a change from -2, current level of function to 0, expected level of performance) [53].

#### Secondary outcomes

##### The box & block test (BBT)

The BBT is a brief assessment of hand function, in which the participant is required to transfer as many blocks as possible from one box to another, with one hand, in 60 seconds [54]. Whilst this is a gross assessment of hand function, the BBT provides a standardised assessment of grasp and release, which are important components of hand function. Evidence supports the validity, test-retest reliability and interrater reliability [55] of the BBT [54]. Previous studies suggest that a change score of 4 blocks per minute over a 2 week treatment timeframe represents clinically significant change [55]. It is unknown whether repeating the BBT within a one hour timeframe (for RCT1) will have a practice effect.

##### Wrist joint range of motion

Active and passive joint range of motion of wrist extension (with fingers in a resting position) and Volkmann’s angle (with fingers in extension) will be measured. Measurement will be taken using a device to enable assessors to use a consistent amount of force when taking wrist measurements, given that goniometry measurement of wrist extension has been shown to have moderate interrater reliability [48]. Children will be seated at the edge of a table, with their forearm flat on the wrist device. The palm will be placed on the wrist device and 1kg of force applied to the wrist into extension. To decrease measurement error, a digital inclinometer will be used to verify the measurement (degrees), and a still photograph taken of the inclinometer reading. To measure active wrist extension, the child’s hand will be unstrapped from the device, with the forearm staying in same position as passive range of motion. The child will be asked to extend their wrist, and a demonstration of wrist extension with the fingers flexed will be given. Volkmann’s angle is a measure of digitial flexor tendon tightness [56]. That is, a measure of wrist extension with the fingers held in extension. This measurement will be taken with the child seated, with the forearm strapped into the device as detailed above. With the wrist in flexion, the fingers of the hand will be extended, then the wrist extended to its maximum range without compromising finger extension. As in the other measurements described above, a digital inclinometer will be used to measure range of motion.

### Adverse events

Adverse events, including pain, skin irritation and discomfort will be collected and recorded at each outcome measure timepoint. If adverse events relate to the use of the hand splint, the hand splint will be modified or use discontinued. If significant or unintended adverse events occur, parents will be encouraged to have the child reviewed by a medical practitioner.

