### Study procedures

Figure 1 depicts the study procedure. Informed consent will be obtained following screening for eligibility criteria. Baseline assessment, using the COPM, GAS, BBT and wrist range of motion will be completed within 3 weeks of treatment (T1). Following baseline assessment, participants will be randomly allocated to one of 3 treatment groups:

1. Functional hand splint alone.

2. Task-specific training (CO-OP) combined with functional hand splint.

3. Task-specific training (CO-OP) alone.

Participants allocated to a group involving a functional hand splint will have a customised hand splint fabricated immediately following randomisation. One hour following baseline assessment, the box and blocks test will be repeated with participants allocated to the functional hand splint alone (with splint on) or task-specific training alone (no splint) group (T2). This data will be used to investigate the immediate effect of a functional hand splint (RCT1). All participants will then undertake 2 weeks of treatment, according to group allocation. The functional hand splint alone group will be expected to wear the splint for 1 hour of daily practice of goals. Task-specific training will involve 10 daily one hour sessions of CO-OP conducted over 12 consecutive days. CO-OP will be undertaken within a group of 2-4 participants. Children allocated to the task-specific training (CO-OP) combined with functional hand splint will be expected to wear their hand splint at all times during the 10 sessions of CO-OP. Assessment at the end of the 2 weeks of treatment (T3) will involve the COPM, GAS, Box and blocks test and wrist range of motion. Log books of home practice will be completed by all participants. Participants will not be expected to continue practice of goals beyond the 2 week treatment timeframe. Participants will be asked to complete a log book of practice if they choose to continue to utilise the functional hand splint or practice goals using those strategies from CO-OP intervention. Follow up assessment, using the primary outcomes only (COPM and GAS) will occur at 10 weeks following baseline assessment (T4).

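### No scheduled adverse-event collection falls within the two weeks of prescribed splint wear, so problems from repeated wear are first asked about on schedule at T3 (a minor gap)

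*Protocol article*

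**What the plan says.** The Adverse events section sets the schedule: "Adverse events, including pain, skin irritation and discomfort will be collected and recorded at each outcome measure timepoint". If an event relates to the splint, "the hand splint will be modified or use discontinued". For significant or unintended events, parents are encouraged to seek medical review. Neither action is tied to a visit.

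Study procedures gives the timing:

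- Baseline (T1) is completed within 3 weeks of treatment.
- Children in a splint group "will have a customised hand splint fabricated immediately following randomisation".
- For T2: "One hour following baseline assessment, the box and blocks test will be repeated with participants allocated to the functional hand splint alone". The training-alone group is also tested then. No T2 assessment is described for the combined group.
- During treatment: "The functional hand splint alone group will be expected to wear the splint for 1 hour of daily practice of goals". Combined-group children wear the splint throughout their 10 training sessions, held over 12 consecutive days.
- T3 is at the end of the 2 weeks of treatment, and T4 is 10 weeks after baseline. After treatment: "Participants will not be expected to continue practice of goals beyond the 2 week treatment timeframe".

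All participants complete log books, described as records of home practice. Under Interventions, a parent or carer must attend every training session. Under Blinding, assessors do not look at log books.

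**The concern.** Pain, skin irritation and discomfort are the events the article itself names. They can develop with repeated wear, and mild ones can clear within days. If families are first asked on schedule when prescribed wear is ending, an event that came and went may be forgotten or given the wrong date, and the record of splint-related harm may be incomplete. There is also a small safety side. Modifying the splint is most useful while the child is still wearing it. In the splint-alone group, a problem comes to light before T3 only if the family raises it.

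The stake is the completeness of the harm record, plus a modest gain in protection for children wearing the splint at home. The efficacy analysis is not involved.

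**Working it through.** The plan gives no figure to reproduce. The check sets the stated timepoints against the period of splint wear.

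**Inputs**

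- Timepoints T1 to T4: Abstract and Study procedures.
- Splint made after randomisation, which follows baseline: Study procedures.
- T2 placed 1 hour after baseline (Study procedures) or 1 hour after randomisation (Abstract).
- Wait from baseline to treatment of 0 to 21 days: the 3-week limit in Study procedures.
- Treatment period of 2 weeks = 14 days: Interventions.
- 15 children per group in three groups: Trial design.

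**Step 1. What each timepoint can show about the splint**

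| Timepoint | Splint exposure by then | What scheduled inquiry can detect |
|---|---|---|
| T1 | None | Nothing about the splint |
| T2 | Under 1 hour (splint-alone group only) | An immediate fit problem |
| T3 | The whole prescribed course | Events still present, or remembered |
| T4 | No further wear expected after T3 | Nothing new about prescribed wear |

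The T2 limit holds whichever reference point is used. The splint is made after randomisation, so part of the hour goes on making it.

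**Step 2. Collection points inside prescribed wear.** Timepoints strictly between T2 and T3: 0.

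**Step 3. Length of the gap**

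- Calendar interval T2 to T3 = wait + treatment = (0 to 21) + 14 = 14 to 35 days.
- Part of that interval with prescribed wear = at most 14 days.

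The 14 days is the relevant figure. The extra 0 to 21 days come before treatment, when no wear is prescribed.

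**Step 4. Exposure that T2 does not cover.** For the splint-alone group, reading daily practice as every day, prescribed wear is 14 × 1 hour = 14 hours, all after T2. For the combined group it is 10 sessions × about 1 hour = about 10 hours.

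**Step 5. Children concerned**

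- Splint wearers: 15 + 15 = 30 of 45.
- Combined group: 15, seen in the splint at 10 therapist-led sessions with a parent present. Recording of adverse events at those sessions is not stated.
- Splint-alone group: 15, with no contact described between T2 and T3.

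**Step 6. Missed events.** The article gives no event rate, so the number of events missed or misdated cannot be estimated.

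**The case against.** The strongest reply is that the schedule is a minimum. A reader might infer that adverse events are collected only at the timepoints, but the text does not say so and does not exclude events reported or seen in between. The rule to modify or stop the splint points the other way: since prescribed wear ends at T3, the rule has little use unless problems are handled during wear. This stands. The point can only be about when families are first asked on schedule.

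A reader might also infer that everything learned at T3 rests on memory. That goes too far: an event still present at T3 can be seen or reported as current. Recall matters only for events that have resolved, and up to two weeks is not a long period to ask about.

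A third reply is that the article condenses a fuller protocol, and that log-book content, family instructions or a reporting route may be set out there. This stands as a limit on the remedy, which is needed only if those items do not already exist. It does not remove the point, because the article states a collection schedule and that schedule has no point within the period of wear.

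Finally, combined-group children wear the splint in front of a therapist and a parent, known allergy to thermoplastic is an exclusion, and the splint-alone dose is 1 hour a day. All of this is correct and keeps the expected harm low. None of it provides scheduled inquiry or described contact for the splint-alone children during their wear.

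**Conclusion.** The point holds as a minor weakness in how harms are collected. On the stated schedule, problems that develop with repeated wear are first asked about at T3, up to 14 days after prescribed wear began, and mild events that have resolved by then may be missed or misdated. This applies to the 30 splint wearers and most to the 15 in the splint-alone group.

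It rests on two assumptions: that splint wear follows the prescribed pattern, and that no between-visit recording is set out in a document not shown.

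Two stronger readings should be avoided. One is that recall spans 35 days: that figure includes up to 21 days before treatment with no prescribed wear. The other is that splint problems go unmanaged until T3: the modify-or-discontinue rule is not tied to visits, and families can report at any time. No efficacy estimate, power or error rate is affected. It is an improvement worth considering.

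**What to change.** If it is not already there, add to the log book a dated adverse-event entry covering pain, skin irritation, discomfort and action taken, running from splint fitting onward. For splint families, print an instruction to stop wearing the splint and contact the treating therapist if a problem occurs. In the Adverse events section, state that these entries supplement collection at the timepoints and that the treating therapist, not the blinded assessor, handles them. For the combined group, the therapist can look at the entries during sessions.

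The cost is slightly more form completion for families and some therapist time to deal with reports. No visit is added, and assessor blinding is not threatened because assessors already do not see the log books. The change has a limit: in the splint-alone group, detection before T3 still depends on the family making contact. The gain is a dated record made at the time and a clear instruction on what to do.
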